### Study outcomes

The overall objective of AGEP was to make a meaningful change in the traditionally observed trajectories of vulnerable adolescent girls in Zambia as they pertained to early family formation, low schooling attainment and poor sexual and reproductive health. The process of change was posited to advance in phases, with the more immediate changes in the girls’ assets and empowerment deriving from their participation in AGEP, translating into positive behavioural change and, ultimately, to longer-term change over the course of four years in which empowered adolescents would realize more positive transitional outcomes. As the concept of empowerment, mediating and longer-term outcomes are potentially broad and multifaceted, a set of representative indicators was used to epitomise their operationalization in the evaluation as noted in Table 4. The indicators of empowerment ranged across the broad domains of social, economic and health and included measures of self-efficacy, social connections, positive gender normative beliefs, financial literacy, access to savings and sexual and reproductive health knowledge, among others. The longer-term indicators of programme impact ranged across three domains, socio-demographic, educational and health.

**Table 4 Tab4:** Primary and secondary study outcome indicators and measures

Immediate programme outcomes	Asset domain
Percentage of girls with high self-efficacy	Social
Percentage of girls with strong role models and social support	Social
Average number of friends, friends who can be counted on	Social
Percentage of girls who hold positive gender normative believes	Social
Average score on financial literacy scale	Economic
Percentage of girls who have opened a formal bank account	Economic
Average score on knowledge of sexual reproductive health	Health
Average number of modern contraceptives known	Health
Percentage having comprehensive knowledge of HIV	Health
Percentage of girls accessing sexual and reproductive health services	Health
Mediating outcomes indicators	
Percentage of girls working for cash or in-kind in the past year	Economic
Percentage of girls with a modest amount of savings	Economic
Percentage of girls who have used a condom during last sex with a non-marital/non-cohabiting partner	Sexual and reproductive health
Percentage of girls who are using modern contraception	Sexual and reproductive health
Percentage of girls who have engaged in transactional sex	Sexual and reproductive health
Longer-term outcomes indicators	Outcome domain
Percentage of girls ever married	Socio-demographic
Percentage of girls ever pregnant and given birth	Socio-demographic
Percentage of girls experiencing unwanted pregnancy	Socio-demographic
Percentage of girls completing grade 7 and grade 9	Educational
HIV prevalence among girls	Sexual and reproductive health
Herpes Simplex Virus Type-2 (HSV-2) prevalence among girls	Sexual and reproductive health

### Hypotheses

The study will test several hypothesis to assess the impact of AGEP and its components. The hypothesis tests reflect the causal pathways as illustrated in the theory of change (Fig. 1). The impact of the intervention is posited to have operated through four general and domain-specific mechanisms, 1) by improving factual knowledge and building skills, 2) increasing self-confidence and efficacy, 3) increasing adolescent aspirations and motivations and, 4) improving access to key resources and services. The first set of hypotheses reflect the expectation that AGEP is having a strong and positive effect on the array of assets that girls can build upon and utilize to affect change. These are measured as immediate programme outcomes indicators in Table 4. A second set of hypotheses is made regarding the impact of the intervention on what are conceptualized here as mediating factors, reflected through HIV and pregnancy risk reduction behaviours, improved attendance in school and possessing greater economic resources and opportunities. The indicators used to reflect these hypotheses are presented as mediating outcomes indicators in Table 4. Finally, the overall objective and ultimate goal, of the programme is to improve the wellbeing of adolescent girls, reflected in specific ways, by reducing early marriage, early pregnancy and births, increasing educational attainment and reducing the acquisition of HIV and the Herpes Simplex Virus Type – 2 (HSV-2).

#### Weekly girls groups meetings

As noted above, all three intervention arms included weekly meetings in which girls met with a mentor and each other to engage with a curriculum topic for the week, generally discuss their experiences and to socialize with each other. Given the randomized design, it is possible to assess the impact of the girls groups alone. The weekly girls’ group meeting is hypothesized, in particular, to have positive effects on the girls’ sexual and reproductive health, financial and nutritional knowledge, as well as build their communications, money management and self-advocacy skills. The group meetings also targeted the girls’ social assets, including the number of friends reported, the quality of those relationships and whether they report a role model in their lives. Participation in the groups is also hypothesized to reduce social isolation and provide access to community spaces. These relationships and opportunities are, in-turn, hypothesized to weaken regressive gender norms and roles, move aspirations, and improve mediating behaviours, such as attending school. In the domain of schooling attainment, these changes are hypothesized to improve school participation, performance and, ultimately, attainment. If confirmed, these hypothesizes will result in strong and positive relationships between the indicator of randomization to the girls group only study arm and the indicators noted along this continuum of outcomes.

#### Health voucher

As with the bank account component, the health voucher intervention is hypothesized to directly increase access to health facilities and resources, as well as to increase efficacy and decision-making control over the utilization of health facilities and resources. The effect of the heath voucher component is expected to be distinguishable empirically over and above what is realized through the weekly girls groups alone. In the immediate term, the health voucher is hypothesized to increase the use of sexual and reproductive health services, including the use of modern contraception. Improved sexual and reproductive health, e.g., by obtaining counselling, care and treatment for STIs, is hypothesized to reduce HIV acquisition in the longer-term, while access to contraception is hypothesized to reduce unwanted pregnancy and birth outcomes. In general, it is hypothesized that as specific health issues are prevented or resolved, girls will have more positive assessment of their overall health.

#### Bank accounts

As noted in Table 1 above, the weekly girls’ group curriculum includes 19 sessions on setting financial goals, budgeting and managing savings and expenditures. While the lessons themselves are hypothesized to directly increase knowledge and improve financial and entrepreneurial aspirations, the bank account component of AGEP was designed to provide a direct link and access to financial services to catalyse change. It is hypothesized, therefore, that the provision of a bank account will have positive impact on informal and formal savings behaviour. Increased access and control over economic resources is hypothesized to reduce the need for adolescent girls to rely on household resources from which they have less control to obtain personal items such as clothing and hygiene products, schooling supplies and/or pay school fees. Access to bank accounts is also hypothesized to depress the need for adolescent girls to rely on older and potentially riskier partners and exchange-based sexual relationships. These changes are hypothesized to reduce the prevalence of sexual exchange and, ultimately, reduce girls’ acquisition of sexually transmitted infections, including HIV and HSV-2.

### Research population and sample sizes

Participants for the research study were randomly selected among all invited AGEP participants who were never married at baseline, stratified by site and age group. For comparability, selection of the control girls followed a parallel process for identifying and selecting vulnerable girls, specifically a ranking of girls by their vulnerability score and randomly selecting girls below a set threshold, with the threshold determined by the total number of girls needed for recruitment into the programme at each site. As the ultimate objective of the funder and the programme was to improve the well-being of adolescent girls, the longer-term outcomes in Table 4 served as the focal indicators for the sample size calculations. As limited evidence was available for a sample size determination based on known effect sizes, minimally detectable effects were estimated using Optimal Design Plus Software Version 3.0 for a multi-site randomized trial to determine the most efficient sample size (number of clusters and respondents per cluster) given the budget available for fieldwork [25]. Sample sizes were estimated for the evaluation after four years, with conservative estimates of attrition, 20% for the younger cohort and 35% for the older cohort. The samples were stratified by the younger and older cohorts (10–14 and 15–19) and urban and rural. The age stratification was necessary as there was no age mixing of groups in the weekly girls groups and certain aspects of the curricula were adjusted for age-appropriateness by cohort.

The minimally detectable effect sizes were estimated for comparison of each programme component against the control; estimates of effect sizes were not obtained for comparisons between the intervention arms themselves as little prior information was available to guide such an estimation approach. Given a total of ten study sites, it was determined that a total of 40 clusters per arm (four clusters per arm per site) and 20 participants per cluster was the most efficient combination. Baseline (control) estimates of study indicators by age group and residential status were obtained from the 2007 Zambia Demographic and Health Survey [26]. Statistical power of 0.80 and an alpha coefficient of 0.05 were set, while the effect size variability was fixed at 0.00, as analyses would control for site fixed effects [25]. Table 5 provides estimates of prevalence in the control sample and minimal detectable effect sizes, by outcome and study stratifications.

**Table 5 Tab5:** Estimates of prevalence in the control and minimally detectable effect sizes in percentage points (pp) of programme impact by age-cohort and by rural and urban stratifications

	Total^a^		Rural^b^		Urban^b^	
	Younger	Older	Younger	Older	Younger	Older
Ever had sex	40%, ± 10 pp	82%, ± 9 pp	47%, ± 14 pp	89%, ± 11 pp	34%, ± 13 pp	75%, ± 13 pp
Ever married	15%, ± 6 pp	63%, ± 10 pp	19%, ± 11 pp	76%, ± 13 pp	10%, ± 8 pp	48%, ± 14 pp
Ever given birth	16%, ± 6 pp	70%, ± 10 pp	18%, ± 10 pp	83%, ± 13 pp	13%, ± 8 pp	54%, ± 14 pp
Completed grade 7	61%, ± 10 pp	60%, ± 9 pp	43%, ± 14 pp	41%, ± 15 pp	79%, ± 11 pp	85%, ± 9 pp
Completed grade 9	28%, ± 10 pp	38%, ± 10 pp	11%, ± 11 pp	17%, ± 13 pp	45%, ± 15 pp	64%, ± 14 pp
Ever use of modern contraception	15%, ± 8 pp	55%, ± 7 pp	15%, ± 12 pp	55%, ± 14 pp	15%, ± 12 pp	55%, ± 15 pp
HIV prevalence	6%, ± 4 pp	12%, ± 6 pp	6%, n/a ^c^	7%, n/a ^c^	6%, n/a ^c^	19%, ± 10 pp
HSV-2 prevalence	21%, ± 8 pp	26%, ± 8 pp	21%, ± 11 pp	26%, ± 12 pp	21%, ± 11 pp	26%, ± 12 pp

*Notes*: Younger cohort members are expected to be ages 14–18 at endline; older cohort members are expected to be ages 19–23 at endline. All estimates assume alpha of 0.05, power of 0.80, and site fixed effects

^a^For each age cohort estimates are based on: 10 sites, 4 clusters per arm per site (40 clusters per arm), and 10 subjects per cluster

^b^For each age cohort estimates are based on: 5 sites, 4 clusters per arm per site (20 clusters per arm), and 10 subjects per cluster

^c^Not powered at 0.80 to detect programme impact

The sample size calculations indicated that 3200 girls would be needed at the end of the study to assess all key study impact indicators: 800 girls (within 40 study clusters) in each of the three AGEP arms and in the control arm. An additional 400 girls (within 20 clusters) were designated to be sampled for urban areas in nearby high-density components. These girls and clusters were designed to serve as external controls given the potential for contamination between AGEP and control girls within the same site. Never married girls were targeted at baseline as a significant proportion of older girls would have already experienced the key outcomes that were meant to be impacted by the programme. To achieve the target sample of 3600 girls at the end of the study, the sample size was inflated for non-eligibility and non-response at baseline, attrition from the cohort and refusals for biological specimen collection. Thus, the final estimated sample to be collected at baseline was 7200 or 4800 in AGEP clusters, 1600 in internal control clusters and 800 in external control areas.

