### Randomised cluster design

The AGEP evaluation was designed as a multi-arm randomised cluster trial where clusters within the ten study sites were randomised to receive different combinations (arms) of AGEP. The experimental and control arms of the study are displayed in Table 3, along with their associated components. Clusters assigned to the first intervention arm were assigned only the weekly girls’ group sessions. Clusters in the second intervention arm were assigned the health voucher in addition to the weekly girls’ group sessions, while clusters in the final intervention arm were assigned all components, including the bank account. The multi-arm evaluation provided for a rigorous assessment of the marginal benefit, as well as the incremental cost-effectiveness of each additional component of the intervention. All girls selected for participation in AGEP within a cluster were assigned to the intervention that was randomly selected for that cluster; girls in clusters for the control arm received neither interventions nor placebo exposures.

**Table 3 Tab3:** Randomisation arms of AGEP

Study arm	AGEP components
Intervention arm 1	Weekly girls group mentor-led sessions
Intervention arm 2	Weekly girls group mentor-led sessions + health voucher
Intervention arm 3	Weekly girls group mentor-led sessions + health voucher + bank account
Control	No components of the AGEP intervention

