### Analysis

The primary objective of the evaluation is to assess the impact of AGEP on adolescents’ intermediate empowerment and longer-term outcomes using the above-noted hypothesis as test criteria. Important as well, analysis will be conducted to understand the underlying processes by which change occurred in the key areas of interest. As a first approach for assessing the impact of AGEP on empowerment and longer-term outcomes, an intent-to-treat analysis (ITT) will be conducted using the original randomised assignment to study arm as the primary indicator of impact. The average treatment effect of the programme on the adolescents in clusters randomised to AGEP relative to girls in clusters randomised to the control will be empirically assessed. The analysis will estimate models that are both unadjusted and adjusted for baseline covariates; both approaches accounting for strata and intraclass correlations within clusters. To accommodate for any baseline differences between AGEP and control clusters that may exist in the outcomes, a difference-in-differences (DID) calculation will be made for each indicator. The mid-term assessment after Round 3 focused on the immediate and mediating indicators as primary outcomes, while in the final assessment after Round 5 the mediating and longer-term outcomes will be the empirical focus.

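### Table 5's detectable effects leave almost no room for correlation within the randomised areas, and five of its 45 cells miss 80% power even with none

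*Protocol article*

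**What the plan says.** All references are to the protocol article.

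- **Randomised cluster design:** "clusters within the ten study sites were randomised to receive different combinations (arms) of AGEP". The clusters are CSAs.
- **Research population and sample sizes:** "Statistical power of 0.80 and an alpha coefficient of 0.05 were set, while the effect size variability was fixed at 0.00"; the reason given for the zero is that site fixed effects would be in the models. Each programme arm is sized against control.
- **Table 5, notes:** the Total columns rest on "10 sites, 4 clusters per arm per site (40 clusters per arm), and 10 subjects per cluster", and the Rural and Urban columns on "5 sites, 4 clusters per arm per site (20 clusters per arm), and 10 subjects per cluster". The notes add: "All estimates assume alpha of 0.05, power of 0.80, and site fixed effects". Three HIV cells carry footnote c, which marks them as not reaching 0.80. The other 45 cells print a control rate and a detectable effect.
- **Analysis:** the intent-to-treat models are fitted unadjusted and covariate-adjusted, "both approaches accounting for strata and intraclass correlations within clusters".

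**The concern.** When areas are randomised, the error of an arm comparison includes the correlation between girls in the same area. With 10 girls per cluster even a modest ICC enlarges the detectable effect. The planned test allows for that correlation, so the sizing should too. Table 5's effects sit at or just above the values for independent girls, and a few sit below them.

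The section Evaluation methods and design claims power for each component, separately in rural and urban areas. A null result at Round 5 will be read against these printed effects. If they are too small, it could be taken to rule out effects that the trial had limited power to detect.

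**Working it through.** **Inputs (Table 5 and its notes).** Girls per arm per age cohort: n = 40 × 10 = 400 (Total) or 20 × 10 = 200 (Rural, Urban). Alpha is 0.05, read as two-sided because the effects are printed with ±. Power is 0.80, so the multiplier is 1.96 + 0.84 = 2.80. These are end-of-study sizes, so attrition is not applied again. The effect d is taken in the hypothesised direction: a fall for sex, marriage, birth, HIV and HSV-2, and a rise for grades 7 and 9 and contraception.

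**Formulas.** With control rate p, q = p ± d and V = p(1−p) + q(1−q):

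- detectable effect for independent girls: the d that solves d = 2.80 × √(V/n)
- power = Φ(d/√(V × DE/n) − 1.96), with DE = 1 + 9 × ICC
- implied DE = (d/2.80)² × n/V; implied ICC = (DE − 1)/9

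**Step 1: reproducing the table with independent girls.** Ever married, older cohort:

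| Column | Control | Printed | Independent girls |
|---|---|---|---|
| Total | 63% | 10 pp | 9.7 pp |
| Rural | 76% | 13 pp | 12.8 pp |
| Urban | 48% | 14 pp | 13.7 pp |

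Over the 45 cells the median implied DE is 1.13 (interquartile range 1.05 to 1.17). The median implied ICC is about 0.015 (0.006 to 0.019), and 39 of 45 cells lie at or below about 0.025. The two outliers are ever married, younger: Rural (19%, ±11 pp) at 0.04 and Urban (10%, ±8 pp) at 0.05. No single ICC reproduces every cell. A pooled-variance formula gives nearly the same picture: median 0.014, best single fit about 0.01, and an ICC of 0.05 matching only 2 of 45 cells.

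**Step 2: cells that miss 80% with no clustering (DE = 1, n = 400).**

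| Cell | Printed | V | d/√(V/400) | Power | Detectable |
|---|---|---|---|---|---|
| Contraception, Total older | 55%, ±7 | 0.483 | 2.01 | 52% | 9.7 pp |
| Given birth, Total younger | 16%, ±6 | 0.224 | 2.53 | 72% | 6.6 pp |
| Married, Total younger | 15%, ±6 | 0.209 | 2.62 | 75% | 6.4 pp |
| Grade 7, Total older | 60%, ±9 | 0.454 | 2.67 | 76% | 9.4 pp |
| HSV-2, Total older | 26%, ±8 | 0.340 | 2.74 | 78% | 8.2 pp |

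In all five the opposite direction gives lower power. The last three fall within rounding of the printed effect to a whole point. The first two do not, although birth exceeds 6.5 pp only narrowly and would just reach 80% if its control rate had also been rounded up from 15.5%. The contraception cell also conflicts with its own row. Rural ±14 and Urban ±15 at the same 55% imply 14/√2 = 9.9 and 15/√2 = 10.6 for twice the sample, so about ±10 and not ±7.

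**Step 3: power at the printed effects over assumed ICCs.** The article gives no ICC, so these are assumptions.

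| ICC | DE | Median power | Cells below 80% (of 45) |
|---|---|---|---|
| 0 | 1.00 | 85% | 5 |
| 0.01 | 1.09 | 81% | 18 |
| 0.02 | 1.18 | 78% | 35 |
| 0.05 | 1.45 | 70% | 44 |
| 0.10 | 1.90 | 58% | 45 |

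At ICC 0.02, 0.05 and 0.10 the detectable effect for ever married, older, becomes 10.6, 11.7 and 13.4 pp (Total, printed 10) and 14.8, 16.3 and 18.5 pp (Urban, printed 14).

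**The case against.** **Clustering may have been in the calculation.** The article says that the software was used to choose the number of clusters and of respondents per cluster. A reader might infer from the effect size variability of 0.00 that clustering was ignored. The text does not support that: the term describes how the treatment effect varies between sites and is not the between-cluster ICC. The objection stands on that point. The table's arithmetic still shows that whatever ICC was used was close to zero.

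**The ICC may be in the full protocol.** An article may leave it there, so its absence is not the point. The printed effects are, and no unseen text changes them.

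**The loss of power rests on an assumed ICC.** This stands for 40 cells. At 0.01, 27 of 45 cells still reach 80%. It does not touch the five cells in step 2.

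**Other features could recover power.**
- Covariate adjustment may help, but the sizing credits only site fixed effects, and unadjusted models are also planned.
- The baseline target of 1,600 per arm is 40 girls per cluster, about 20 per cohort if split equally. After 20% and 35% attrition alone that leaves 16 and 13 girls, and median power for the survey outcomes at ICC 0.05 would be about 79%. This is an upper bound, because the same inflation also covers non-eligibility and baseline non-response, whose rates are not given.
- Pooling the three programme arms against control would give a median of about 84% at ICC 0.05, but Table 5 sizes each arm separately.

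**One-sided alpha.** A one-sided 0.05 would raise the median implied ICC to about 0.047, but the ± points to a two-sided test.

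**Conclusion.** The concern holds in a limited form. Without any ICC assumption, five of the 45 cells fall short of the 0.80 that the table note claims for all estimates. Contraception, Total older, is clearly wrong at 52%; birth, Total younger, is beyond rounding of its printed effect; the other three could be rounding.

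The remaining 40 cells are sound only if the within-site ICC is very small, with a median tolerance of about 0.015. Whether they fail is not known from the article. A reader might conclude that the trial as a whole does not deliver 80% power, but the document does not support that, because it gives no ICC. The sensitivity is considerable all the same: median power goes from 81% to 58% as the assumed ICC goes from 0.01 to 0.10. These figures rest on two-sided alpha, 10 girls per cluster per cohort, equal cluster sizes, each arm against control and no gain from covariates.

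**What to change.** 1. Correct the five cells in step 2, starting with contraception, Total older.
2. Recompute Table 5 with an explicit within-site, between-CSA ICC for each outcome, and state it in the table note. Round 3 control-arm data can supply it, or baseline data where the outcome varies at baseline. That excludes ever married, because the sample was restricted to never-married girls. Where no estimate is available, show a stated range such as 0.01 to 0.10.
3. For each cell, restate either the effect detectable at 80% power or the power at the effect now printed, and apply footnote c to cells below 0.80.

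The cost is a recalculated table and a sentence on the ICC. No extra enrolment or design change is needed. The downside is that the stated detectable effects become larger and more cells may carry footnote c.

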## Background

This paper reviews the design and methods of a multi-arm, randomized cluster evaluation of the Adolescent Girls Empowerment Programme (AGEP) in Zambia. The programme was designed as a multi-sectoral intervention targeted to vulnerable, rural and urban adolescent girls ages 10–19. Embedded in the design of the programme was a rigorous, randomized evaluation that recruited a cohort of eligible adolescent girls invited to participate in the programme and girls residing in control areas. The evaluation sample was interviewed at baseline in late 2013 and early 2014 and is being tracked annually through 2017, with mid-term results collected in 2015 immediately after the end of the intervention and endline results in 2017, two years post programme termination [1].

Adolescent girls in less developed countries face a variety of risks and challenges in achieving positive and successful transitions to adulthood [2]. In Zambia, a significant proportion of girls enter marriage and/or begin childbearing early, even prior to the expected age of school leaving. As indicated by the 2013–2014 Zambia Demographic and Health Survey (DHS), nearly one in three girls aged 20–24 had married by age 18, with a similar percentage having begun childbearing [1]. The prevalence in rural areas is nearly double that of urban areas for both early marriage (39% versus 22%) and early childbearing (42% versus 21%) [3]. Not surprisingly, given rates of early marriage and childbearing, the risk of school leaving for girls during the school age years is high, with 18% of primary school age girls and 59% of secondary age girls not currently attending school [1]. The Zambia DHS also indicates that girls in Zambia begin sexual activity early, have low rates of condom use and have risk behaviours that increase their chances of acquiring sexually transmitted infections (STIs), including HIV. For instance, the median age of sexual debut is 17.7 years, approximately 1 year prior to marriage, and the prevalence of sexual initiation among 15–19 year olds is 27%. Further, of those who are currently engaging in premarital sexual activity, only 36% reported using a condom at last sex. The low rate of consistent condom use implies exposure to STIs, with 4% of adolescents 15–19 reporting having an STI or symptoms of a sexually transmitted disease and 5% having acquired HIV. The prevalence of HIV more than doubles by the time girls reach the ages of 20–24 years [1].

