### Girls group meetings

The AGEP intervention operated for a period of two years in each site from late 2013 and early 2014 through late 2015 and early 2016. Implementation of the programme was initiated sequentially by site, after the baseline evaluation survey was completed in each site. The core component of AGEP was group meetings in which 20 to 30 girls met at a local community space for one to two hours per week, most often on weekends. A community-based model was selected as school-based sexual reproductive health programs have been known to have limited impact because teachers find it hard to break out of their typical teaching styles and programs are adversely affected by an already low quality of schooling [13, 14]. In addition, school-based programs exclude out-of-school girls, which were meant to be included in the intervention. The girls’ groups were stratified by age (10–14 and 15–19) and by marital/fertility status; girls stayed with their original groups as they aged or otherwise changed status. The group sessions were based on three core curricula (Table 1) and used illustrative vignettes, role play and participatory methods to maximize impact. The meetings were led by an older, young woman from the community who had been trained to initiate and guide educational sessions and exercises on a variety of subjects. The mentors were trained in groups at central locations at the beginning of the programme, with one refresher training approximately one year into the program. Monthly mentor meetings also took place with site coordinators to address mentor questions, experiences and provide short reviews of curriculum topics.

**Table 1 Tab1:** AGEP core curricula implemented through weekly girls’ groups meetings

Health and life skills	Session topics
Introductory sessions (9 sessions)	What to expect (×2 sessions); teamwork; gender roles; communication; self-esteem; goal identification; goal setting; personal relationships
Reproductive health (9 sessions)	Life cycle; body changes; pregnancy; avoiding unintended pregnancy; reproductive myths; sexual desire; unsafe abortion, abortion and stigma; maternal mortality
Life skills (11 sessions)	Healthy relationships; reasons for delaying sex; strategies for delaying sex; passive, assertive and aggressive behaviour; drugs and alcohol; peer-pressure; decision-making; communications; managing emotions; conflict resolution

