AGEP was also designed to draw participants who expressed multiple levels of vulnerability through their residential location and the socio-economic characteristics of their households. To avoid over-representing girls in AGEP who have already experienced the outcomes that were to be prevented by the programme (early marriage, becoming pregnant, dropping out of school), these indicators were not directly used to identify vulnerability. Instead, an indicator of vulnerability was created using whether girls were behind in school for their age as a proxy, which also permits characterization of the vulnerability of girls younger than those who already have been married, pregnant or dropped out of school. Conceptually, the measure captures adolescents who are at risk of adverse outcomes, given the primacy of education in a child’s life at these ages. Early in the school-going process, many children fall behind in school due to late entry, repetition of grades, and temporary withdrawal from school; all of these events are a reflection of some degree of personal and household vulnerability. The information used to develop the measure of vulnerability was collected along with other household socio-economic characteristics via a household survey in all study clusters, which was subsequently used as a sampling frame to determine eligible girls for participation in the programme with the most vulnerable girls selected from the list to receive invitations to participate.

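### Screening on marriage alone leaves girls with a prior birth in the 15–19 cohort, so the ever-given-birth outcome dilutes the first-birth effect the study says it was powered for

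*Protocol article*

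**What the plan says.** All references are to the protocol article.

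- **Who is studied** (Research population and sample sizes): participants were "randomly selected among all invited AGEP participants who were never married at baseline, stratified by site and age group". The reason given is "Never married girls were targeted at baseline as a significant proportion of older girls would have already experienced the key outcomes".
- **The outcome** (Study outcomes, Table 4): a longer-term indicator is "Percentage of girls ever pregnant and given birth". The sample-size section says that "the longer-term outcomes in Table 4 served as the focal indicators for the sample size calculations", and Table 5 has its own row for ever given birth. The abstract lists first birth among the outcomes the study was powered for.
- **Selection into the programme** (Intervention population): of marriage, pregnancy and school drop-out it says "these indicators were not directly used to identify vulnerability".
- **Grouping** (Girls group meetings): groups were formed by age "and by marital/fertility status; girls stayed with their original groups as they aged or otherwise changed status".
- **Analysis** (Analysis section): intent-to-treat by assigned arm, with and without adjustment for baseline covariates, plus a difference-in-differences calculation for every indicator.

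No section excludes girls who have already been pregnant or given birth, or limits the birth outcome to girls who have not.

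**The concern.** The stated reason refers to key outcomes in the plural, but the criterion acts on one of them. Marriage is an incomplete screen for childbearing in this setting. The Background reports that "the median age of sexual debut is 17.7 years, approximately 1 year prior to marriage", so sexual activity commonly begins before marriage.

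An ever-outcome cannot reverse. A girl with a birth before Round 1 is positive at every round whichever arm she is in, and the programme cannot change that. Including her has two effects: the percentage-point difference is averaged over girls who could not respond, and the quantity estimated differs from an effect on first birth. The first effect makes a null result more likely on one of the study's headline outcomes.

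**Working it through.** **1. Is marriage an incomplete screen?** Table 5 gives control estimates for ever given birth (B) and ever married (M). Even if every ever-married woman had given birth, the share of never-married women with a birth would be at least (B − M)/(100 − M).

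| Stratum | B | M | Minimum share of the never-married with a birth |
|---|---|---|---|
| Older, total | 70 | 63 | 7/37 = 19% |
| Older, rural | 83 | 76 | 7/24 = 29% |
| Older, urban | 54 | 48 | 6/52 = 12% |
| Younger, total | 16 | 15 | 1/85 = 1% |
| Younger, urban | 13 | 10 | 3/90 = 3% |
| Younger, rural | 18 | 19 | no positive bound |

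These are endline ages (19–23 and 14–18). They show that marriage does not capture all births, but they do not measure the share at baseline.

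**2. Reproducing the plan's figure.** Table 5 gives ±10 pp for ever given birth in the older cohort, total sample: control 70%, 40 clusters per arm with 10 girls each (400 per arm), alpha 0.05, power 0.80. The intraclass correlation (ICC) and sidedness are not stated; I assume a two-sided test. With effective n = 400/(1 + 9 × ICC) and the pooled-variance formula for two proportions,

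power = Φ{[d − 1.96 √(2p̄(1 − p̄)/n)] / √([p₁(1 − p₁) + p₂(1 − p₂)]/n)},

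the minimum detectable decrease is 9.4 pp at ICC 0, 9.8 pp at 0.01, 10.0 pp at 0.014 and 10.3 pp at 0.02. So ±10 pp fits an ICC of about 0.014, which I use below (design effect 1 + 9 × 0.014 = 1.126, effective n = 355).

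**3. Dilution.** Let q be the share of the older cohort with a birth at Round 1, and let the true reduction be 10 pp among the other girls. Hold the overall control rate at 70%.

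- *Whole-sample endline comparison:* 70% against 70 − 10(1 − q). At q = 10%: 70% against 61%.
- *Individual change-score difference-in-differences:* a girl with a baseline birth has change zero, so new births are compared over all girls, (70 − 100q)% against (70 − 100q)% − 10(1 − q) pp. At q = 10%: 60% against 51%.
- *Restricted to girls with no birth at Round 1:* control rate (0.70 − q)/(1 − q), reduction 10 pp, n = 400(1 − q) per arm, cluster size 10(1 − q). At q = 10%: 66.7% against 56.7%, n = 360, design effect 1 + 8 × 0.014 = 1.112.

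| Assumed q | Whole-sample difference | Power, whole sample | Power, change-score | Power, restricted | Minimum detectable effect, restricted |
|---|---|---|---|---|---|
| 0% | 10.0 pp | 79.9% | 79.9% | 79.9% | 10.0 pp |
| 5% | 9.5 pp | 75.9% | 73.6% | 77.3% | 10.35 pp |
| 10% | 9.0 pp | 71.4% | 67.6% | 74.5% | 10.7 pp |
| 19% | 8.1 pp | 62.5% | 58.1% | 69.2% | 11.4 pp |

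The gain from restriction over the whole-sample comparison is 77.3 − 75.9 = 1.4, 74.5 − 71.4 = 3.1 and 69.2 − 62.5 = 6.7 points. Over the change-score analysis it is 3.7, 6.9 and 11.1 points.

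**The case against.** **The plan is internally consistent.** Table 4 defines an ever-percentage, Table 5 powers the same quantity, and the analysis is intent-to-treat on the same girls. On this view a restricted analysis changes the estimand rather than correcting an error, and at-risk sets can be left to an analysis plan that is not shown. This stands in part: the whole-sample percentage is a legitimate target and should be kept. It does not settle the matter, because the abstract says the study was powered for first birth and the indicator measures something else.

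**The difference-in-differences deals with it.** Only partly. It removes baseline prevalence from the contrast, but the denominator still contains girls who could not respond, so the factor (1 − q) remains.

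**The criterion's wording allows a partial screen.** This stands. The sentence says that never-married girls were targeted and why; it does not claim that every prior outcome is removed. The criterion also lowers the share with a prior birth. A reader might infer an outright contradiction, and the text does not go that far.

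**Most of the lost power cannot be recovered.** This stands too. It comes from having fewer girls at risk, which no analysis filter changes. A reader might set a diluted 9 pp against the tabulated ±10 pp and conclude that restriction would bring the effect back within reach. It would not: the restricted set's own minimum detectable effect is also above 10 pp.

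**Conclusion.** The point holds as a mismatch between the criterion and the first-birth question, with a modest cost in power. It concerns the 15–19 cohort and should be negligible for girls aged 10–14 at baseline.

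Three stronger readings are not supported:

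- **Bias between arms.** Girls with prior births are expected in all randomised arms, so the whole-sample comparison is valid for its own target. The loss is dilution.
- **That 12% to 29% of the older cohort were already mothers.** Those figures describe never-married women aged 19–23, a small remainder once most have married. They do not bound the share at 15–19, which the document does not report.
- **That grouping by fertility status shows how many unmarried mothers were studied.** It shows only that fertility status was expected to vary within the programme.

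The size rests on assumptions: q between 5% and 19%, an ICC of about 0.014 inferred from Table 5, a two-sided test, a 70% overall control rate, and an effect confined to girls without a prior birth. Under these, power for a true 10 pp reduction falls from 80% to between 76% and 63%. Restriction brings it to between 77% and 69%.

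**What to change.** 1. For the first-birth outcome, analyse girls in all arms with no birth recorded at Round 1; for first pregnancy, those with no pregnancy recorded at Round 1. Say how a girl who is pregnant at Round 1 with no earlier birth is handled in the first-birth analysis.
2. Report the whole-sample intent-to-treat percentage alongside it.
3. In Research population and sample sizes, state that the never-married criterion removes prior marriage only, and lowers but does not eliminate prior births.
4. Restate the Table 5 minimum detectable effect for ever given birth in the older cohort using the at-risk number and rate (about 10.7 pp if q = 10%), and report q by arm from Round 1.

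Recruitment does not change. The filter uses baseline status, which the planned difference-in-differences for every indicator already requires, and each site's baseline survey was completed before the programme began there. The cost is a somewhat smaller analysis set, for example 360 rather than 400 per arm at q = 10%. Under the assumptions above, power is still higher than in either whole-sample analysis.
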